**Primary objectives**

To discover whether:

1. there is agreement between the physiotherapist and the surgeon regarding selection of shoulder patients appropriate for subacromial injection.
2. care (subacromial corticosteroid and local anaesthetic injection) delivered by the physiotherapist is no worse than the same type of care delivered by the orthoapaedic surgeon, with respect to safety, access, effectiveness and efficiency.

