## Statistical Analysis

All statistical analyses will be performed on an intention to treat basis using the statistical package SPSS (V19.0, IBM, New York, USA), with alpha level set at 0.05.

The analysis of the GEE will be conducted using SAS Statistical Software version 9.2.

**Stage 1:**  Agreements between the decisions from the two clinician assessors will be investigated using the proportion of observed agreement, the probability of chance agreement, and the kappa statistics with the 95% confidence intervals.

**Stage 2:** For continuous outcomes, normality of data will be assessed and parametric tests applied if normality is upheld. Treatments from the two clinicians will be compared over time (pre- to post-intervention) on an intention-to-treat basis using the generalised estimating equation (GEE) approach (Liang and Zeger1986) with an exchangeable working correlation structure to account for within-subject correlation for repeated measurements. With the GEE, a normal distribution with an identity link will be used for continuous outcome measures. The respective pre-condition baseline scores will be included as a covariate. The effects of time (within-group differences), practitioner (between-group differences), and practitioner by time interaction (between-group differences over time) will be included in all models and assessed using the Wald χ2 test. Model fit and assumptions will be checked were appropriate within the GEE framework. The GEE approach works well with missing observations on outcome measures, assuming that they are missing completely at random (MCAR). The validity of this assumption will be examined. If the MCAR assumption was violated, adjustment using weighted GEE (Hogan et al., 2004) will be performed. Appropriate post hoc tests will be conducted if significant main or interaction effects are identified from the omnibus analyses.

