**Sample size:** Assuming α = 0.05, β = 0.2, and a standard deviation of 21.7 points of the change in scores from baseline, we estimate that 54 participants (27 per group) will be required to test for a comparative efficacy between the two treatments with a noninferiority margin of 15 points in the SPADI scores. The above parameter values for the power calculation are based on previous study on comparing the responsiveness for SPADI and several indices in patients receiving corticosteroid injection therapy (Ekeberg et al., 2010), where the minimum clinically important difference (MCID) for the SPADI is 23.1 points at 6 weeks. The calculation is conservative in the sense that it ignores the added power inherent in the repeated measures design. However, it is appropriate when treatment comparisons at the two individual time points (6 weeks and 12 weeks) are performed to assess the interaction treatment effect at different time after the injection. Allowing for a conservative drop-out rate of 15%, we will recruit a total of 64 participants (32 per group) for stage 2. In order to obtain this number, we anticipate needing 128 recruits into stage 1 because we estimate that 50% of stage 1 participants will be eligible to enter stage 2.

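### Stage 2 asks a noninferiority question with a 15-point SPADI margin, but the planned analysis only tests for a difference and never compares the result with that margin

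*Protocol*

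**What the plan says.** Under Primary objectives, the protocol sets out to discover whether care "delivered by the physiotherapist is no worse than the same type of care delivered by the orthoapaedic surgeon". In the outcome measures table SPADI is marked as the Stage 2 primary outcome, collected at 6 and 12 weeks.

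The Sample size paragraph asks for 27 per group "to test for a comparative efficacy between the two treatments with a noninferiority margin of 15 points in the SPADI scores". Its inputs are given as "Assuming α = 0.05, β = 0.2, and a standard deviation of 21.7 points of the change in scores from baseline".

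The Stage 2 paragraph of Statistical Analysis describes a GEE with a normal distribution, identity link and baseline score as covariate. Time, practitioner and practitioner-by-time effects are the hypotheses to be tested: the "practitioner by time interaction (between-group differences over time) will be included in all models and assessed using the Wald χ2 test", "with alpha level set at 0.05". It then adds: "Appropriate post hoc tests will be conducted if significant main or interaction effects are identified from the omnibus analyses".

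That paragraph does not mention noninferiority, the margin, or a confidence interval for the difference between clinicians. The only confidence intervals in the section belong to the Stage 1 kappa statistics. The Data Safety monitoring section allows stopping when the treatments are convincingly not different, again without reference to the margin.

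**The concern.** A Wald χ² test has zero difference as its null hypothesis. A noninferiority claim needs the opposite null, that the physiotherapist is worse by 15 points or more, and has to reject it. The objective and sample size pose the second question, while the analysis section answers the first.

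This is more than detail that a protocol may leave to a statistical analysis plan, because the protocol does fix the test and that test does not address its own objective. A later plan that followed the section faithfully would inherit the mismatch. One that added a margin rule would have to go beyond what the section sets out.

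At stake is the main efficacy conclusion. If the two clinicians perform alike, the practitioner and interaction tests will usually be non-significant, and the protocol gives no rule for moving from there to a finding of no worse. The failure to find a difference also becomes more likely as the data become noisier or fewer, which is the wrong direction for a noninferiority claim.

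**Working it through.** **Inputs.** From the Sample size paragraph: margin 15, SD of change 21.7, α 0.05 (sidedness not stated), power 80%, 27 per group, 15% drop-out. A true difference of 0 for the sample size is my assumption, as the protocol does not state it. Differences are physiotherapist minus surgeon, taking a higher SPADI as worse; the protocol does not state the scoring direction.

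**Reproducing the stated size.** n per group = 2 × [SD × (z₁₋α + z₀.₈₀) / margin]².

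- One-sided 0.05: 2 × [21.7 × (1.645 + 0.842) / 15]² = 25.9, so 26. The t-based version gives 27, with power 80.6%, which is the stated figure.
- One-sided 0.025, or a two-sided 0.05 test of a 15-point difference: 2 × [21.7 × (1.960 + 0.842) / 15]² = 32.9, so 33 (34 by t).
- Drop-out: 54 / 0.85 = 63.5, so 64, as stated.

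The 27 per group is therefore a one-sided 0.05 noninferiority calculation. It is not the size for the two-sided difference test in the analysis section.

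**What the planned test can tell us.** SE = 21.7 × √(2/27) = 5.91. The Wald test is non-significant for any observed difference up to 1.96 × 5.91 = 11.6 points.

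- P(non-significant) at true deficit d = Φ(1.96 − d/SE) − Φ(−1.96 − d/SE)
- P(margin test passes) = Φ((15 − d)/SE − z₁₋α)

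| True deficit (points) | Wald test non-significant | Margin test passes, one-sided 0.05 (90% CI) | Margin test passes, one-sided 0.025 (95% CI) |
| --- | --- | --- | --- |
| 0 | 95.0% | 81.5% | 71.9% |
| 5 | 86.5% | 51.9% | 39.5% |
| 10 | 60.5% | 21.2% | 13.3% |
| 15 | 28.1% | 5.0% | 2.5% |

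Using a t distribution with 52 degrees of freedom, the non-significant figures at 15 and 10 points are 29.7% and 61.7%. With all 32 recruited per group evaluable, the figure at 15 points is 21.0% (normal approximation).

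**Where the two readings part.** Noninferiority needs an observed deficit below 15 − 1.645 × 5.91 = 5.3 points with a 90% interval, or below 15 − 1.96 × 5.91 = 3.4 points with a 95% interval. An observed deficit between 5.3 (or 3.4) and 11.6 points is non-significant and yet does not show noninferiority. With no true difference at all, that happens in 16% of trials (90% interval) or 26% (95% interval).

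These figures use one time point and the SD of change, as the Sample size paragraph does. They take no credit for baseline adjustment or repeated measures. Both could shrink the SE and the percentages, but neither changes which null hypothesis is tested.

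**The case against.** The strongest defence is that the parts needed are nearly all present. The margin is stated and drives the sample size. The GEE, with identity link and practitioner terms in every model, yields an adjusted between-clinician difference and its standard error whatever the p-values. The Sample size paragraph also envisages comparisons at 6 and 12 weeks without making them conditional. A decision rule could sit in an analysis plan that is not shown. All of this stands, and it makes the repair easy. It does not supply the missing step, because the protocol's own analysis section names other tests and no passage says what result would show that care is no worse.

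Several stronger readings are tempting but not supported:

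- *The protocol treats a non-significant test as proof of noninferiority.* It does not say so. It gives no rule at all, and the risk is that a reader supplies this one.
- *The margin plays no part, or the contrast is never produced.* The margin sets the sample size and the model produces the estimate. Only the comparison of the two is absent.
- *A clinically trivial difference could count as failure.* Significance needs about 11.6 points observed, and a physiotherapist disadvantage of that size would fail a margin test too.
- *A non-significant result could hide a deficit beyond the cited minimum clinically important difference.* At the limit of non-significance the upper 95% bound is 2 × 11.58 = 23.15, against 23.1, so the point rests on a rounding margin.
- *Intention-to-treat analysis alone invalidates the claim.* The protocol says "All statistical analyses will be performed on an intention to treat basis", which can favour noninferiority. But the injection follows randomisation at the same visit, and a per-protocol set that drops patients with later treatment brings its own bias. This is a separate and debatable matter.

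**Conclusion.** The point holds: the objective and sample size are for noninferiority, and the tests fixed in the analysis section are for a difference. As written, no planned test can establish the second primary objective on SPADI. If non-significance were taken as a substitute, a true deficit at the margin would slip through about 28% of the time (30% by t) instead of 5%, and a true 10-point deficit about 60% of the time instead of about 21%. These sizes rest on 27 evaluable per group, SD 21.7 and a single time point. The mismatch itself rests on no numerical assumption. It should be corrected before the analysis, because it concerns the primary efficacy conclusion and costs very little to put right.

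**What to change.** In the Stage 2 paragraph of Statistical Analysis:

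1. State that the baseline-adjusted physiotherapist-minus-surgeon SPADI difference from the GEE will be reported with its confidence interval whatever the omnibus results.
2. State that noninferiority is declared only if the upper limit is below +15, and that a higher SPADI is worse.
3. Name the primary time point: 6 weeks, 12 weeks, or both required.
4. Name the interval level. A two-sided 90% interval (one-sided 0.05) matches the stated 27 per group at about 80% power. With a 95% interval, power at 27 per group has to be restated as about 70–72%. Holding 80% would take 66–68 evaluable, or about 78–80 recruited (66/0.85 = 77.6; 68/0.85 = 80).
5. Keep the Wald tests for secondary questions about differences. A per-protocol sensitivity analysis is optional.

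The cost is a paragraph of protocol wording and no new data. No extra participants are needed with the 90% interval. With the 95% interval, the choice is between accepting the lower power openly and recruiting more.

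### The Stage 2 GEE effects are tested with a large-sample Wald chi-square on about 54–64 participants with no small-sample correction named, so the 5% level would be mildly exceeded (minor)

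*Protocol*

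**What the plan says.** All of this is in the protocol's Statistical Analysis section, including its sample size paragraph.

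- **Model.** Continuous outcomes, including the primary SPADI, are analysed by the "generalised estimating equation (GEE) approach (Liang and Zeger1986) with an exchangeable working correlation structure", with a normal distribution, an identity link and the baseline score as covariate. The post-baseline visits are at 6 and 12 weeks.
- **Test.** The effects of time, practitioner and their interaction "will be included in all models and assessed using the Wald χ2 test". The section opens "with alpha level set at 0.05" and does not say whether this is one- or two-sided.
- **Sample size.** "Assuming α = 0.05, β = 0.2, and a standard deviation of 21.7 points of the change in scores from baseline", the plan states that "54 participants (27 per group) will be required", "with a noninferiority margin of 15 points in the SPADI scores". It continues: "Allowing for a conservative drop-out rate of 15%, we will recruit a total of 64 participants (32 per group) for stage 2".

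The section names neither a variance estimator (sandwich or model-based), nor a finite-sample correction, nor a t or F reference. It also does not say how the 15-point margin is to be judged within the GEE.

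**The concern.** The Wald chi-square is justified by a large number of independent clusters. Here each participant is a cluster, and there are 54 to 64 of them. Two things go wrong at that size, both in the same direction. The uncorrected sandwich variance is biased downward because it uses fitted residuals. The chi-square (normal) reference also has thinner tails than the t or F it replaces.

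The effect is that a practitioner difference or interaction is declared significant slightly more often than 5% of the time. The primary question is whether the physiotherapist's care is no worse. If the confidence limit for that question is built from the same standard errors and normal quantiles, it sits slightly too close to the estimate. The error then runs towards declaring non-inferiority, which is the direction such a trial should guard against.

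**Working it through.** **Inputs from the protocol:** SD 21.7, margin 15, alpha 0.05, power 0.80, 27 per group (54), 64 recruited, 15% drop-out, two post-baseline visits, baseline covariate, exchangeable correlation.

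**Assumptions not in the protocol:** a true difference of zero, one-sided alpha 0.05 for the sample size, and for the simulations normal errors, within-subject correlation 0.5 and baseline correlation 0.5.

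**1. The plan's own figure.** n per group = 2·SD²·(z₁₋α + z₁₋β)²/margin².
- One-sided 0.05: 2 × 21.7² × (1.645 + 0.842)²/15² = 25.9, so 26 per group. The t-based version gives 27, with power 80.6%.
- One-sided 0.025: 32.9, so 33 per group (34 with t). This does not reproduce 27.
- Drop-out: 54/0.85 = 63.5, so 64.

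The stated 54 and 64 are therefore reproduced at one-sided 0.05.

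**2. Analytic size of the problem.** Take the uncorrected sandwich standard error as shrunk by f = √((N−p)/N), and a z critical value used where t on N−p degrees of freedom is appropriate. Actual error is then 2·P(t > 1.960·f) two-sided, or P(t > 1.645·f) one-sided.

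| N | p | f | SE shortfall | two-sided 5% becomes | one-sided 5% becomes |
| --- | --- | --- | --- | --- | --- |
| 54 | 3 | 0.972 | 2.8% | 6.25% | 5.8% |
| 54 | 4 | 0.962 | 3.8% | 6.5% | 6.0% |
| 64 | 3 | 0.976 | 2.4% | 6.0% | 5.7% |
| 64 | 4 | 0.968 | 3.2% | 6.25% | 5.8% |

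If the standard error is unbiased and only the reference is wrong (f = 1), two-sided error is 5.5–5.6%.

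**3. Simulation under the null** (20,000–40,000 replicates of the stated GEE).

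| Setting | Shortfall, sandwich | two-sided | one-sided 0.05 |
| --- | --- | --- | --- |
| N = 54, complete | 2.1–3.3% | 6.0–6.4% | 5.6–5.8% |
| N = 64, complete | 2.0–2.4% | 5.9% | 5.6% |
| N = 64, 15% missing at week 12 | 3.6% | 6.5% | 5.9% |

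With model-based standard errors the ratio of estimated to true standard error is 0.99–1.01 and the two-sided error is 5.2–5.9%. In these runs the exchangeable structure was true, which is the condition that model-based standard errors need.

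**4. After correction.**
- Sandwich scaled by N/(N−3) with t on N−3: 4.9–5.1% at N = 54 and 4.8–4.9% at N = 64.
- Mancl-DeRouen type correction with z: 4.7% (N = 54, complete) and 5.3% (N = 64 with missing data).
- The same correction with t: 4.2% and 4.8%, slightly conservative.

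**5. On the SPADI scale.** For a simple two-group comparison, SE = 21.7 × √(2/27) = 5.91. The one-sided 95% half-width is 1.675 × 5.91 = 9.9 points with t on 52 degrees of freedom. With z and a standard error 3.5% too small it is 1.645 × 5.91 × 0.965 = 9.4 points. The limit moves by about 0.5 point against a margin of 15.

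**6. Cost in width.** Widening = (t quantile/z quantile)/f. At the smallest simulated shortfall (2.0%, N = 64, one-sided) it is 1.015/0.980 = 1.036. At N = 54, p = 4, two-sided, it is 1.025/0.962 = 1.065. So intervals become about 4–6% wider.

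**The case against.** The strongest reply is that the variance estimator and finite-sample corrections normally belong in a statistical analysis plan, which may exist and is not shown. A Wald chi-square does not rule out a corrected variance. The effect is also only about one percentage point of error and half a SPADI point of interval width. Most of this stands, and it is why the sandwich figures are stated as conditional and the point is minor. What it does not remove is that the protocol writes down the chi-square reference. That is a choice made, and a later plan using t or F would depart from it.

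Five stronger readings are tempting and are not supported:

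- **That standard errors are 3–4% too small as a matter of fact.** No estimator is named. Citing the paper that introduced GEE makes a sandwich likely, but model-based standard errors largely remove the shortfall. Even with a sandwich, the simulated figure is nearer 2–3% unless data are missing.
- **That the planned tests misjudge the 15-point margin.** The Wald tests address time, practitioner and interaction effects, not the margin, and no confidence limit is specified. The effect on the margin follows only if a limit is built the same way.
- **That the design contradicts itself because 27 per group is t-based.** The protocol gives neither formula nor sidedness. The inference rests on one participant per group, and sizing on a simple comparison before a longitudinal analysis is ordinary.
- **That interim looks make it markedly worse.** Interim analyses are mentioned under Data Safety monitoring without number, timing or method, so any figure would describe an assumed look.
- **That the missing-data step fails.** The protocol says "If the MCAR assumption was violated, adjustment using weighted GEE (Hogan et al., 2004) will be performed" but names no test for the assumption, so a power figure for that check would rest on an invented one. Bias of the exchangeable GEE under missing-at-random drop-out was checked and was at most 0.1 point with equal variances. There is no case here for deleting the step.

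**Conclusion.** The point holds as a minor one. At this size the stated test would run somewhat above its nominal level under either variance estimator, and more so with the uncorrected sandwich, where the nominal 5% becomes about 6.0–6.5% two-sided. These sizes rest on normal errors and on the correlations assumed in the simulations; the analytic calculation does not use those correlations and agrees closely. Calling the level at the margin one-sided 0.05 rests on the sample size arithmetic, since the protocol does not state it. Nothing here calls the planned number of participants into question.

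**What to change.** In the Stage 2 paragraph of Statistical Analysis, keep the GEE and replace the uncorrected Wald chi-square with a small-sample-corrected sandwich variance and a t or F reference. Mancl-DeRouen, Kauermann-Carroll or scaling by N/(N−p) are all suitable corrections. State that the t-based confidence limit for the practitioner difference is the one compared with the 15-point margin. A linear mixed model with Kenward-Roger degrees of freedom is an acceptable alternative but is not needed to cure this defect.

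The cost is a sentence in the protocol and the wider intervals shown above. The planned 27 per group already carries the t allowance: power is 80.6% at one-sided 0.05 under the protocol's SD and margin. Neither the sample size nor the stated 80% power has to change.

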***There is support for the use of corticosteroid injection for shoulder pain***

While many different shoulder management strategies exist, high level evidence does not clearly support any one treatment. Relevant Cochrane reviews provide some limited evidence to support the use of corticosteroid injection, physiotherapy and oral steroids in non-traumatic, non-instability based shoulder pain:

• Corticosteroid injection for shoulder pain (Buchbinder 2009): Subacromial corticosteroid injection for rotator cuff disease and intra-articular injection for adhesive capsulitis may be beneficial although their effect may be small and not well-maintained.

• Physiotherapy for shoulder pain (Green 2010): There is some evidence from methodologically weak trials to indicate that some physiotherapy interventions are effective for some specific shoulder disorders. The results overall provide little evidence to guide treatment.

• Oral steroids for adhesive capsulitis (Buchbinder 2009): oral steroids provides significant short-term benefits in pain, range of movement of the shoulder and function in adhesive capsulitis but the effect may not be maintained beyond six weeks.

• Acupuncture for shoulder pain (Green 2008): Due to a small number of clinical and methodologically diverse trials, little can be concluded from this review.

• Surgery for shoulder osteoarthritis (Singh 2010): No studies compared shoulder surgery to sham surgery, non-surgical modalities or placebo. Total shoulder arthroplasty seems to offer an advantage in terms of shoulder function, with no other clinical benefits over hemiarthroplasty.

• Surgery for rotator cuff disease (Coghlan 2009): No firm conclusions about the effectiveness or safety of surgery for rotator cuff disease. Three trials compared either open or arthroscopic subacromial decompression with active non operative treatment (exercise programme, physiotherapy regimen of exercise and education, or graded physiotherapy strengthening program). No differences in outcome between these treatment groups were reported in any of these trials.

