Similar to many musculoskeletal conditions and perhaps in response to the lack of evidence supporting any one treatment strategy, many shoulder services pragmatically offer a variety of treatments. This multimodal approach is advocated by the UK National Institute of Clinical Excellence, whose national clinical guidelines for the management of Osteoarthritis in Adults (2008), recommends the use of combined physical and pharmaceutical measures, including intra-articular corticosteroid injection as an adjunct to other treatment for the relief of moderate to severe pain.

Crawshaw (2010) in a pragmatic randomised controlled trial recently tested this multimodal approach by comparing corticosteroid injection combined with exercise and manual therapy to exercise and manual therapy alone, in 232 patients with subacromial impingement syndrome. The combined injection and physiotherapy group was significantly better at on the primary outcome measure (SPADI) at week 1 and week 6, however there was no significant difference by week 12. There was still a higher complete recovery rate in the combined group at week 12. At week 24 more patients in the exercise only group continued to take painkillers and went on to seek an injection after their 12 week course of treatment ended.

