*** primary outcome measure stage 1**

**^ primary outcome measure stage 2**

| **Category** | **Measure** | **From** | **Timing** |
| --- | --- | --- | --- |
| **Clinical and Demographic Characteristics** | Age, sex, employment status, hand dominance, uni or bilateral | Participant | Baseline |
| Imaging to date and key findings | Referral | Baseline |
| Duration of symptoms | Participant | Baseline |
| Past treatments and costs – physiotherapy, injection, surgery, other | Participant | Baseline |
| Medications | Participant | Baseline |
| **Baseline outcome measures** | Impact and costs questionnaire | Participant | Baseline |
| Work Productivity and Activity Impairment Questionnaire (WPAI) | Participant | Baseline |
| Work Limitations Questionnaire (WLQ) | Participant | Baseline |
| Shoulder Pain and Disability Index (SPADI) | Participant | Baseline |
| 10 cm VAS patient perception of pain over the past 3 days | Participant | Baseline |
| EuroQual-5D-5L | Participant | Baseline |
| **Stage 1** | | | |
| **Clinical agreement** | Are there any safety contraindications to injection? | Clinicians | At time of assessment |
| Are there any safety precautions regarding injection? | Clinicians | At time of assessment |
| *** Would you provide subacromial injection today?** | Clinicians | At time of assessment |
| Are there any other reasons to exclude this participant from stage 2 | Clinicians | At time of assessment |
| **Stage 2** | | | |
| **Safety** | Incidence of adverse events | Adverse event reporting mechanism | Collated throughout |
| **Access** | Current new appointment booking dates with Orthopaedics and OPSC | Research Assistant | At time of intervention |
| **Effectiveness** | **^Shoulder Pain and Disability Index (SPADI)** | Participant | 6 weeks  12 weeks |
| 10 cm VAS patient perception of pain over past 3 days | Participant | 6 weeks  12 weeks |
| Global Rating of Change Scale | Participant | 6 weeks  12 weeks |
| EuroQual-5D-5L | Participant | 6 weeks  12 weeks |
| Physiotherapy attendances post injection | eMR / Groupwise | 6 weeks  12 weeks |
| 10 cm VAS patient satisfaction with care | Participant | 12 weeks |
| **Economic** | Staff costs for each clinician | Standard pay scales | 6 weeks  12 weeks |
| Impact and costs questionnaire | Participant | Baseline |
| Work Productivity and Activity Impairment Questionnaire (WPAI) | Participant | Baseline |
| Work Limitations Questionnaire (WLQ) | Participant | Baseline |

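### SPADI is primary at both 6 and 12 weeks, but the protocol names no time, contrast or success rule for the stage 2 non-inferiority decision, so the stated alpha and power are undetermined

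*Protocol*

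**What the plan says.** In the protocol's table of outcome measures, the row "Shoulder Pain and Disability Index (SPADI") carries the symbol for the stage 2 primary outcome. Its timing cell lists 6 weeks and 12 weeks, and neither is singled out.

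The sample size paragraph under Statistical Analysis is built on one comparison: "Assuming α = 0.05, β = 0.2, and a standard deviation of 21.7 points of the change in scores from baseline", "with a noninferiority margin of 15 points in the SPADI scores", leading to 27 per group (54) and to 64 after 15% drop-out. It describes this size as conservative because it ignores the gain from repeated measures, and as appropriate when "treatment comparisons at the two individual time points (6 weeks and 12 weeks) are performed to assess the interaction treatment effect". The only planning figure tied to a visit is the statement that the "MCID) for the SPADI is 23.1 points at 6 weeks".

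The stage 2 analysis text plans a GEE with baseline score as covariate and Wald tests of time, practitioner and their interaction. Post hoc tests follow only if one of these is significant. Alpha is given once, for everything: "with alpha level set at 0.05". Sidedness is not stated.

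On how long the injection effect lasts, the background section reports that in the cited trial of injection plus exercise and manual therapy against exercise and manual therapy alone, the injection group did better "on the primary outcome measure (SPADI) at week 1 and week 6, however there was no significant difference by week 12". It also says that complete recovery was still more frequent with injection at week 12. The cited review of subacromial injection says that it "may be beneficial although their effect may be small and not well-maintained". Under Interventions, both arms are offered physiotherapy from one week after injection.

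**The concern.** A non-inferiority claim needs a defined decision: one contrast, at a stated time or averaged over stated times, whose confidence limit is set against the margin. This protocol supplies a margin and a sample size, but two primary visits and no rule linking them. None of the three Wald tests is a comparison with 15 points, so the analysis text does not supply the rule either.

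Two things are at stake.

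- **Error and power.** If success at either visit is enough, the chance of wrongly declaring the physiotherapist no worse exceeds the nominal level. If both visits must succeed, power is below what was planned. Left open, the choice could be made after the results are seen.
- **What a week-12 result means.** If injection adds little on SPADI over physiotherapy by week 12, two injectors of unequal skill will tend to look alike by then. Non-inferiority at that visit would be easier to meet and weaker evidence of equal care.

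**Working it through.** **Inputs from the protocol (sample size paragraph):** SD of change 21.7, margin 15, alpha 0.05, power 0.80, 27 per group, drop-out 15%.

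**Assumptions:** true difference 0 for power; the same SD at both visits; correlation ρ between the 6- and 12-week group differences. The protocol does not give ρ, so it is shown from 0 to 0.9, with 0.5 to 0.8 as the working range.

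**Step 1: reproduce the stated size for one comparison.** n per group = 2(z₁₋α + z₀.₈)² × SD² / margin².

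- One-sided 0.05: 2 × (1.645 + 0.842)² × 21.7² / 15² = 25.9, so 26. The noncentral t version gives 27 with 80.6% power, which matches the protocol.
- One-sided 0.025: 33 (normal) or 34 (t), which does not match.
- Drop-out: 54 / 0.85 = 63.5, so 64, which matches.

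The stated size is therefore right for a single comparison at one-sided 5%.

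**Step 2: standardised distance to the margin with 27 per group.** SE = 21.7 × √(2/27) = 5.906, and 15 / 5.906 = 2.540. Power at one visit by the normal method is Φ(2.540 − 1.645) = Φ(0.895) = 81.5%.

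**Step 3: two visits.** Φ₂ is the bivariate normal distribution function.

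- Either visit suffices, true difference exactly at the margin at both: error = 1 − Φ₂(1.645, 1.645; ρ).
- Both visits required, true difference 0 at both: power = Φ₂(0.895, 0.895; ρ).

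| ρ | Either-visit error | Both-visits power | n per group for 80% under both-visits rule | Recruited at 15% drop-out |
| --- | --- | --- | --- | --- |
| 0 | 9.75% | 66% | 36 | 85 |
| 0.5 | 8.8% | 71% | 34 | 80 |
| 0.7 | 8.0% | 73% | 32 | 76 |
| 0.8 | 7.5% | 75% | 31 | 73 |
| 0.9 | 6.8% | 77% | 30 | 71 |

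**Step 4: alternatives.**

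- Splitting alpha (one-sided 0.025 per visit) controls the error, but power per visit falls to 72% (normal) or 70% (t).
- One practitioner effect averaged over both visits keeps alpha at 5%. Its SE is multiplied by √((1 + ρ)/2). At ρ = 0.5, 2.540 / 0.866 − 1.645 = 1.288, or about 90% power. At ρ = 0.8, 2.540 / 0.949 − 1.645 = 1.032, or about 85%.

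The protocol's remark that the size is conservative is thus true for an averaged contrast and false for a both-visits rule.

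**The case against.** **The GEE already gives one practitioner effect across visits.** On this reading the visit-specific comparisons only follow up an interaction, alpha stays at 5% and power is about 85% to 90%. This stands as a possible reading, and it is why the stated figures are undetermined and not simply wrong. But the protocol never names that effect as the non-inferiority contrast, and the sample size paragraph defends its figure for comparisons at the individual visits.

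**The error figures are a worst case.** This stands. The 8.8% to 7.5% applies only if the physiotherapist is exactly 15 points worse at both visits. The 71% to 75% ignores any gain from baseline adjustment, so it may be somewhat low.

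**The statistical analysis plan may settle it.** That document is not at hand. The primary time decides what the margin and sample size refer to, so it belongs with them in the protocol, which addresses the time and leaves it open.

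**Week 12 still carries information.** A reader might infer from the cited trial that a 12-week comparison cannot reveal a poor injection. The protocol does not support that. A non-significant difference in one trial is not evidence of no effect, and the same trial still had more complete recovery with injection at week 12. The protocol's objective concerns care, and the injecting clinician also decides ongoing management, so differences there, or harm, could appear at week 12. The review's description of the effect as possibly small gives no visit and bears on week 6 as well. Choosing week 6 therefore lessens the sensitivity problem but does not remove it.

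**Conclusion.** The point holds as an undefined primary decision. Two visits are marked primary, the size is for one comparison, and no time, contrast or success rule is given.

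The size of the consequence depends on the rule eventually applied. At one-sided 5%, 27 per group and an assumed ρ of 0.5 to 0.8:

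- success at either visit: false non-inferiority of up to 8.8% to 7.5%, against a nominal 5%;
- success at both visits: about 71% to 75% power, against about 81%;
- a single visit, or one pre-named averaged contrast: alpha as stated and at least the stated power.

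Over ρ from 0 to 0.9 the direction does not change: error 9.75% to 6.8%, power 66% to 77%. One-sided 5% is inferred from the sample size and is not stated in the protocol.

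On week 12, the supported conclusion is doubtful sensitivity of SPADI to injection quality. It rests on one trial's non-significant difference and on physiotherapy being offered to both arms, and it goes no further than that.

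**What to change.** Name the between-group SPADI difference at 6 weeks, estimated from the baseline-adjusted GEE, as the single primary stage 2 contrast. State that the 15-point margin and the 54/64 sample size apply to it, and that alpha is one-sided 5%. Make SPADI at 12 weeks secondary, reported as an estimate with confidence interval and without a stand-alone non-inferiority claim.

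Three places must agree: the marked row of the outcome table, the stage 2 analysis text (which must name the 6-week contrast and not leave it to post hoc tests after a significant Wald test), and the sample size paragraph. Six weeks suits the cited evidence and the visit of the quoted MCID.

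The cost is wording only. The stated size remains valid and no data collection changes. What is lost is a confirmatory claim at 12 weeks.

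Two other rules would also remove the ambiguity. A both-visits rule would have to state its lower power, or be re-sized to 34 to 31 per group (80 to 73 recruited) for ρ of 0.5 to 0.8. A pre-named visit-averaged contrast would keep alpha and power, but would mix in the visit at which sensitivity is doubtful.
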